## Abstract

**Background:**

Non-ST segment elevation acute coronary syndrome has been one of the most serious diseases threatening human health. Long-term cardiac rehabilitation and secondary prevention is the essential method to control the recurrence and mortality of the disease. Traditional Chinese medicine has proved the efficiency on the treatment of non-ST segment elevation acute coronary syndrome, but there is a lack of appropriate methodological design to reflect the characteristics of individualized diagnosis and treatment of it. Therefore, this study used the evidenced-based Goal Attainment Scale to evaluate the clinical effectiveness of traditional Chinese medicine on the treatment of non-ST segment elevation acute coronary syndrome.

**Method:**

This is observational research with the prospective feature. A total of 200 patients will be recruited and observed in the three months by telephone or door visit, collecting the individualized intervention of traditional Chinese medicine and evaluating through the method of evidence-based Goal Attainment Scale. Participants will be included according to the inclusion and exclusion criteria. Any reasons for loss to follow-up and adverse events will be recorded strictly. *Discussion*. The evidence-based Goal Attainment Scale provides a personalized method of evaluation based on the Goal Attainment Scale and combined with evidence-based medicine, which can better reflect the characteristics and superiority of individualized and dynamic intervention for traditional Chinese medicine on the long-term prevention and treatment of non-ST segment elevation acute coronary syndrome than other methods of design. It is of great significance to explore and promote this method of design in the future.

## 1. Introduction

Non-ST segment elevation acute coronary syndrome (non-ST-elevation ACS, NSTE-ACS) is a clinical syndrome in which patients have acute chest pain but no sustained ST-segment elevation in electrocardiogram [1]. The clinical spectrum ranges from no symptom to persistent ischemia, instability of electrophysiology or hemodynamics, or cardiac arrest. The incidence of NSTE-ACS has increased in recent years, and the proportion is higher than that of ST-segment elevation acute coronary syndrome (STE-ACS) [2], which constitutes acute coronary syndrome (ACS) with NSTE-ACS together. Since the wide disease spectrum, neuromas complications, and difficult diagnosis in the early stage are the characteristic of NSTE-ACS, positive and effective diagnosis and treatment of it attached great importance in clinical practice [3]. Although the prognosis and long-term survival of patients with NSTE-ACS have improved significantly with the method of early assessment and advance of interventional therapy based on risk stratification and the standardized drug therapy, long-term cardiac rehabilitation and the secondary prevention after the acute phase has become the key to control the recurrence and mortality of cardiac events [4].

Traditional Chinese medicine (TCM) has a history of thousands of years and obtains a unique understanding and methods of therapy for various diseases. According to the clinical manifestations, NSTE-ACS belongs to the category of “Xiong Bi (chest pain)”, “Xin Ji (palpitation),” and “Zhen Xin Tong (pain of the heart)” for TCM's theory [5]. The field of advantage for TCM applied to clinical treatment lies in chronic noncommunicable diseases, which represent that this kind of treatment has certain advantages according to the long-term period individualized intervention. In recent years, the clinical efficacy of TCM, which is categorized as complementary and alternative medicine, has been continuously proved in the treatment of NSTE-ACS [6]. Clinical treatment of TCM belongs to a personalized medical practice model under the guidance of syndrome differentiation, and its clinical efficacy has been verified for thousands of years. However, there is a lack of scientific and standardized methodological design to support the acquisition of individualized evidence of TCM, which is limited in the progress of international promotion and application [7]. It is urgent to establish a method of evaluation for clinical efficacy that conforms to the characteristics of individualized diagnosis and treatment of TCM and in line with current international clinical standards [8].

Goal Attainment Scale (GAS) is a method of evaluation in order to quantify progress toward defined rehabilitation goals [9]. Its principle is to set a number of indicators for specific individuals, calculating the total score and giving each individual the final points through the 5-level Likert scale to evaluate the realization of each index quantificationally. This method could maintain comparability between the individual on the premise of different indexes. Evidence-based GAS is a personalized method of evaluation based on GAS and combined with an evidence-based medicine analysis model, aiming at the individualized trend of clinical evaluation for TCM, which has been highly recognized in China [10]. Both evidence-based GAS and TCM have the same aspect of paying attention to the experience of doctors and the feeling of patients; however, evidence-based GAS is much more objective and convincing than the traditional methodology of TCM for evaluation.

This study protocol was based on the empirical observational research, adopting the method of evidenced-based GAS and collecting the information of diagnosis and treatment about the TCMs individualized therapy of NSTE-ACS, to evaluate the clinical effectiveness and variation of therapy for TCM objectively.

## 2. Methods

### 2.1. Objectives

The objective of this research is to evaluate the individualized clinical efficacy of TCM in the quantitative way (evidence-based GAS) by long-term observing the variation of symptoms and the corresponding adjustment of prescriptions after the individualized treatment of TCM on NSTE-ACS.

### 2.2. Study Setting and Trial Design

This is observational research which will conduct at the Dongzhimen Hospital Affiliated to Beijing University of Chinese Medicine (BUCM), the Third Affiliated Hospital of BUCM, and the Beijing Hospital of Traditional Chinese Medicine Affiliated to Capital Medical University. This research has a prospective feature, which means that the admission period of patients will be between March 1, 2020, and August 31, 2020. We will include 200 hospitalized patients who were diagnosed as NSTE-ACS. Each included patient will be followed up by telephone or door visit every 2 weeks, collecting the individualized intervention of TCM and evaluating through the table of evidence-based GAS. The whole procedure of the research will consist of 6 times of follow-up. This protocol conforms to the statement of Strengthening the Reporting of Observational Studies in Epidemiology (STROBE) [11] (see Supplementary File 2) and is made some adjustments based on the adaptability for TCM.

### 2.3. Study Participants

#### 2.3.1. Diagnostic Criteria

*Diagnostic Criteria of NSTE-ACS for Western Medicine*. The criteria are based on the 2014 AHA/ACC Guideline for the Management of Patients with Non-ST-Elevation Acute Coronary Syndromes [12]. (a) Clinical symptom: paroxysmal pain in the retrosternal area and can radiate to either both arms, the neck, or the jaw; intermittent or sustainable symptoms of diaphoresis, dyspnea, nausea, abdominal pain, or syncope; unexplained new-onset or increased exertional dyspnea. (b) Physical examination: the emerging of pulmonary rales or S3 might represent cardiac insufficiency due to myocardial ischemia in high-risk patients. (c) Electrocardiogram: ST depression, transient ST elevation, or new T-wave inversion are the changes in ECG in patients with NSTE-ACS. The ECG can be relatively normal or initially nondiagnostic. (d) Biomarkers of myocardial necrosis: cardiac troponins can indicate a myocardial injury and provide information on risk stratification when they rise within a few hours of symptom onset and remain elevated for several days and exceed the 99th percentile of the reference value at least once. (e) Imaging: echocardiography can show the decrease of left ventricular ejection fraction (LVEF) and the decrease or disappearance of myocardial segmental motion. Cardiac magnetic resonance imaging (MRI), myocardial perfusion imaging, and multisource computed tomography (CT) to obtain the value in the diagnosis and exclusion of NSTE-ACS.
*Diagnostic Criteria of NSTE-ACS for TCM*. The criteria are based on the diagnostic criteria of Xiong Bi which come from the diagnostic and effective criteria of TCM [13]. (a) Feeling of precordium pain and can radiate to either or both arms, the neck, or the jaw with intermittent or sustainable characteristics. Patients can be accompanied by palpitations, shortness of breath, sweat, or even dyspnea. (b) Chest pain can be alleviated from a few seconds to tens of minutes. Severe pain can combine with sweat, cold in the limb, pale in the face, cyanosis of the lips and nails, palpitation, or even sudden cardiac death. (c) It can be triggered by overwork, depression, anger, overeating, or catch a cold. (d) Diagnosis can be supported by the examination of ECG, dynamic ECG, treadmill test, or cardiac troponins.

#### 2.3.2. Inclusion and Exclusion Criteria

*Inclusion Criteria*. Participants who meet the following criteria will be included. (a) Male or female patients between 18 years old and 85 years old. (b) Conformed to the diagnosis of NSTE-ACS, including unstable angina and non-ST-segment elevation myocardial infarction (NSTEMI), and complied with the diagnosis of Xiong Bi. (c) Had clearly related symptoms of NSTE-ACS or Xiong Bi and the number of episodes of symptoms more than 2 times per week. (d) Time period of hospitalization between March 1, 2020, and August 31, 2020. (e) Agreed to sign the informed consent (see Supplementary File 1).
*Exclusion Criteria*. Participants who meet any of the following criteria will be excluded. (a) With a cardiogenic shock, heart rupture, or interventricular perforation. (b) Had the history of major organ surgery within one month along with active or tendency of bleeding. (c) Patients with implantable defibrillators or pacemakers. (d) With severe liver and kidney dysfunction, malignant tumor, or endocrine, urinary, blood system, nervous system, and other serious primary diseases. (e) With cardiovascular diseases including acute pericarditis, subacute infective endocarditis, aortic dissection, and/or severe arrhythmia. (f) With a history of serious allergies or allergic to Chinese or western medicine. (g) Female during the stage of pregnancy and breastfeeding stage. (h) Have participated in other clinical trials.

#### 2.3.3. Criteria of Exit, Discontinuance, and Rejection

Patients will exit based on the situation as follows: (a) physicians will make a decision if patients have allergic reactions, serious adverse events, complications, or special physiological changes and were not suitable for this research or have poor compliance affecting clinical judgment. (b) Patients are unable to continue follow-up and file an application. The discontinuance of research is followed by orders from the sponsor or administrative department. The rejection criteria are based on the inclusion and exclusion criteria, insufficient information, or lost to follow-up.

### 2.4. Interventions

This protocol is the observational setting with no controlled group. The method of self-control is used to compare therapeutic efficiency. All included participants will not apply any particular interventions for the aim of scientific research. The tool of evidence-based GAS is the way of analysis and evaluation, which represents patients who can receive the individualized treatment of TCM or western medicine based on their situations. The only requirement is they should choose the TCM or combined therapy if they have a need to be treated by physicians.

### 2.6. Method of Evidence-Based GAS

#### 2.6.1. Importance and Difficulty for the Classification of Weight

This part will be accomplished by patients based on the guidance of researchers. The score of weight that constitutes the evidence-based GAS will be obtained by multiplying the *Importance* times the *Difficulty* (Tables 1 and 2). According to the scoring system, the goal for evaluation will be eliminated if the *Importance* or the *Difficulty* is set as 0. The score of weight is between 1 and 3 points in general. The score of weight will be set as 1 if the physician considers that there is no difference in the score of weight.

#### 2.6.2. Establishment of the Goal of Treatment

The goal of treatment for evidence-based GAS should be consistent with clinical practice. Goals should be set through mutual consultation among physicians, patients, and their families. These goals are people who want to achieve in the course of the treatment. Evidence from the published systematic review and guideline will be used as the support for the establishment of a goal and are listed in Table 2. It is reasonable for most researchers to define the *Baseline* (basic statement before the therapy) at the level of −1 in general unless some symptoms have a greater potential of improvement that can be defined as −2. The formulation of goals should follow the principle named SMART (specific, measurable, achievable, realistic, and timed) which helped physicians shepherd patients to choose realistic goals [14]. Three to five appropriate and reasonable goals will be applied as the basis of evaluation in the final, and the numbers of goals for each individual can be different based on the situation.

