#### 2.6.5. Realistic Results

Professional evaluators will assign corresponding scores according to the completion of each goal at the arranged time point after the therapy. *T* score will be calculated by the difference between the score of baseline and result based on the completion of evidence-based GAS. It will be the final score of a patient to evaluate the characteristics of clinical therapy. Two factors should be taken into account when calculating the score: (1) different weight scores (*w*_*i*_) should be given due to the different degrees of each indicator; (2) the influence of quantity variance should be eliminated due to the number difference of each goal. The formula is listed as follows:(1)$$\begin{array}{c} \text{GAS}=50+\frac{10\sum^{}\left(W_{i}X_{i}\right)}{\sqrt{\left(\left(1-p\right)\sum^{}w_{i}^{2}+p\left(\sum^{}w_{i}^{2}\right)\right)}}. \end{array}$$

Note: *x*_*i*_ represents the score for the indicator of the item *i*; *w*_*i*_ represents the weight for the indicator of the item *i*; *p*=0.3.

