## Figures and Tables

**Figure 1 fig1:**
[figure not shown]
Flow diagram of observational research by the evidence-based Goal Attainment Scale.

**Table 1 tab1:** The classification of score of weight for *Importance* and *Difficulty*.

Importance	Difficulty
0 = not important	0 = not difficult
1 = slightly important	1 = slightly difficult
2 = important	2 = difficult
3 = very important	3 = very difficult

**Table 2 tab2:** The goal of treatment from physicians and evidence-based medicine (3 to 5 goals among the 8 goals can be selected form the table).

Goal of treatment	Importance	Difficulty	Weight	Baseline	Results
1. Whether can improve the symptom of chest pain					
2. Whether can improve the quality of life (based on the SF-36 form)					
3. Whether can reduce the drug use					
4. Whether can reduce finical burden of patients					
5. Whether can improve prognosis of patients based on the report of MACE					
6. Whether can improve the physical-chemical indexes (blood lipids, vascular endothelial function, blood rheologic indexes, oxidative stress, blood routine, liver and kidney functions, and blood coagulation factor)					
7. Whether can improve imaging indexes (LVEF, chest radiography, CT, and MRI)					
8. Whether can improve syndrome efficiency of TCM					
9. Handwritten: the first goal of treatment that patients they want					
10. Handwritten: the second goal of treatment that patients they want					
*Sum of weight*					

**Table 3 tab3:** Scale for evidence-based GAS.

Scale for evidence-based GAS	−2	−1	0	1	2
					
1. Symptom of chest pain	Increase of the frequency of attack and the degree of pain, prolong for duration	No change of the frequency of attack, the degree of pain, and duration	A little bit relieves of the frequency of attack, the degree of pain, and duration	Obvious relieves of the frequency of attack, the degree of pain, and the duration	No any symptoms of chest pain

2. Quality of life based on SF-36 (^1^physiological function, ^2^physical function, ^3^body pain, ^4^general health, ^5^vitality, ^6^social function, ^7^emotional function, and ^8^mental health)	Aggravate obviously for 2 or more among the 8 dimensions of SF-36	No clearly improvement among the 8 dimensions of SF-36	Obvious amelioration for 1 to 2 among the 8 dimensions of SF-36	Obvious amelioration for 3 to 4 among the 8 dimensions of SF-36	Obvious amelioration for more than 4 among the 8 dimensions of SF-36

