3. Situations of drug use	Obvious increase of dosage and categories	No obvious variations for dosage and categories	Decrease of dosage and categories (1 to 2)	Obvious decrease of dosage and categories (more than 2)	Discontinue drug followed by the doctor's advice

4. Financial burden	Obvious increase of financial input	No obvious change of financial input compared with before	Decrease of financial input and relieve of the burden	Obvious decrease of financial input and relieve of the burden	No financial burden

5. Prognosis of patients (MACE: ^1^death, ^2^MI, ^3^stroke, ^4^TIA, ^5^PCI, ^6^peripheral vascular intervention, and ^7^readmission)	1 or more new events (MACE) report compared with before	Events were observed similar to before and no new events report	No event (MACE) reports	No event (MACE) reports for a long time (six months to one year)	No event (MACE) reports for a long time (more than one year)

6. Physical and chemical indicators (^1^blood lipid, ^2^vascular endothelial function, ^3^blood rheologic indexes, ^4^oxidative stress, ^5^myocardial injure marker, ^6^liver and kidney functions, and ^7^blood coagulation factor)	Obvious aggravated more than 2 indicators	No obvious change compared with before	Amelioration of 1 to 2 indicators compared with before	Amelioration of 3 to 4 indicators compared with before	Amelioration of more than 4 indicators compared with before

7. Imaging indexes (^1^LVEF, ^2^chest radiography, ^3^CT, and ^4^MRI)	Obvious aggravated more than 2 indexes	No obvious change compared with before	Amelioration of 1 to 2 indexes compared with before	Amelioration of 2 to 3indicators compared with before	Amelioration of more than 3 indicators compared with before

8. Efficiency of TCM syndrome [13]	Obvious aggravated of the TCM syndrome compared with before	No obvious variation of the TCM syndrome compared with before	A little bit amelioration of the TCM syndrome compared with before	Obvious amelioration of TCM syndrome compared with before	Enormous amelioration of TCM syndrome compared with before

9. Handwriting: the goal 1 that patients want to achieve)					

10. Handwriting: the goal 2 that patients want to achieve					

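### A baseline of −2 on a predefined Table 3 goal credits an unchanged patient with one level of improvement and scores a worsened patient as unchanged

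*Protocol article*

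**What the plan says.** Section 2.6.2 places the baseline ("basic statement before the therapy) at the level of −1 in general"), with an exception: "unless some symptoms have a greater potential of improvement that can be defined as" −2.

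Table 3 prints the five levels for the eight predefined goals. For chest pain (goal 1), level −1 is "No change of the frequency of attack, the degree of pain, and duration" and level −2 is "Increase of the frequency of attack and the degree of pain, prolong for duration". For drug use (goal 3), level −1 is "No obvious variations for dosage and categories". For TCM syndrome (goal 8), level −1 is "No obvious variation of the TCM syndrome compared with before" and level −2 is obvious aggravation. Goals 4, 6 and 7 follow the same pattern, and goal 2 (SF-36) is close to it. Goal 5 (MACE) differs: −1 is events similar to before with none new, and 0 is no events. Handwritten goals 9 and 10 have blank levels.

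Section 2.6.5 states that the T "score will be calculated by the difference between the score of baseline and result based on the completion of evidence-based GAS" and calls this the patient's final score. Section 2.4 says that there is no control group and that patients serve as their own control.

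**The concern.** On a scale whose levels are worded as change from before, the pretreatment state has only one possible position: the unchanged level. For the predefined goals that level is −1. A baseline of −2 would describe a patient who is already worse than his or her own starting point. Nothing in the article rewrites the Table 3 levels when the −2 option is chosen.

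The change score then carries a built-in gain on each affected goal, and that goal has no level left to register worsening. The option is triggered by an expectation of improvement, so the gain falls on the goals where benefit is already anticipated. In a before-after comparison without controls, nothing removes it.

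**Working it through.** The article gives no figure for this point, so there is none to reproduce. The check is of the scoring logic and its size on the GAS scale.

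**Inputs**
- Baseline level: −1 by default, −2 by exception (section 2.6.2).
- Result levels: unchanged = −1, worse = −2 (Table 3, for example goals 1 and 8).
- Score: taken here as result minus baseline, so that improvement is positive (section 2.6.5).
- Goals per patient: 3 to 5 (section 2.6.2).
- Weights: 1 to 3 in general (section 2.6.1). Equal weights of 1 are assumed unless stated.
- p = 0.3 (section 2.6.5).

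**Numerical check of the anchor for goal 8.** Section 2.7.8 gives no obvious variation as a reduction below 30%, and aggravation as a reduction below 0. An unchanged syndrome score is a reduction of 0%, which falls in the first band and not the second. It scores −1.

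**Change on one goal**

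| True course | Result level | Baseline −1 | Baseline −2 |
|---|---|---|---|
| Unchanged | −1 | −1 − (−1) = 0 | −1 − (−2) = +1 |
| Worse | −2 | −2 − (−1) = −1 | −2 − (−2) = 0 |

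The same shift applies to any result x, because x − (−2) = [x − (−1)] + 1.

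**Translation to GAS points.** One affected goal with weight w shifts the difference by 10w/D, where D is the denominator of the formula.
- As printed, both terms under the root contain Σw², so D = √(0.7Σw² + 0.3Σw²) = √Σw². With n weights of 1, D = √n.
- As a sensitivity variant, with the second term read as the square of the summed weights, D = √(0.7n + 0.3n²).

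Artificial gain for an unchanged patient with one goal at −2:

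| Goals | As printed | Squared-sum variant |
|---|---|---|
| 3 | 10/√3 = 5.77 | 10/√4.8 = 4.56 |
| 4 | 10/√4 = 5.00 | 10/√7.6 = 3.63 |
| 5 | 10/√5 = 4.47 | 10/√11 = 3.02 |

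In full for four goals as printed: baseline 50 + 10(−5)/2 = 25.0, unchanged result 50 + 10(−4)/2 = 30.0, difference +5.00.

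**Unequal weights.** With weights 3, 1, 1 and the weight-3 goal at −2, the gain is 30/√11 = 9.05 as printed. In the variant it is 30/√(0.7×11 + 0.3×25) = 30/√15.2 = 7.69.

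**With the baseline at −1 instead.** An unchanged patient has a difference of 0.00. A patient who worsens on one of three goals has −5.77 (printed) or −4.56 (variant). Under a −2 baseline for that goal, the same patient has 0.00.

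**Group level.** If a fraction f of patients have one such goal among four equally weighted ones, the mean shift is 5.00f as printed or 3.63f in the variant. The article does not give f.

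**The case against.** The strongest reply is that GAS levels are set for each individual. Section 2.6.3 has the levels defined after the goal is chosen and asks for clear criteria for every score, and section 2.6.4 refers to detailed setting of each indicator. On that reading Table 3 is a template, and a −2 baseline would come with its own levels. This holds for handwritten goals 9 and 10. It does not hold for the eight predefined goals, whose levels are already printed and tied to change from before. Nor is this a detail left to an analysis plan, since both rules stand in the article.

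Other parts of the reply stand and limit the point:
- The −2 level is an optional exception worded for some symptoms. A reader might infer that the two rules can never coexist, or that all of a patient's goals could start at −2. The default of −1 causes no conflict on the goals with a clean unchanged level, and drug use, cost, MACE, laboratory and imaging goals are not plainly symptoms.
- Success under section 2.6.4 is reaching level 0, which does not depend on the baseline level. The formula has no baseline term, so each follow-up score is unaltered, and so are contrasts among the six follow-ups in the repeated measures ANOVA of section 2.9.
- A reader might infer that deterioration disappears from the study. It does not: sections 2.8.1 and 2.8.4 provide for recording worsening symptoms and adverse reactions, and section 2.7.5 covers MACE. It is lost from the GAS change score for the affected goal.

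**Conclusion.** The point holds in this limited form. Wherever a −2 baseline is used on a predefined goal that has −1 as unchanged, the baseline-to-result difference is one level too high. With one such goal among three to five equally weighted goals, that is 4.5 to 5.8 points by the printed formula or 3.0 to 4.6 in the squared-sum variant. The direction is the same under both readings of the denominator and is always towards apparent benefit.

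It is tempting to go further and set a group-level bias against the precision expected with 200 patients. The documents do not support that comparison, because they give neither the share of goals set at −2 nor a standard deviation. The bias could be negligible if the option is rarely used. The severity is should-fix: the rule as written gives a wrong change score, but only through an optional exception of unstated frequency and only for comparisons with baseline.

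**What to change.** - For predefined Table 3 goals, set the baseline at the level the table defines as unchanged (−1), and delete the −2 exception from section 2.6.2 and the scoring instructions.
- Allow −2 only for handwritten goals 9 and 10, and only where that goal's own levels are written so that −2 describes the actual pretreatment state and an unchanged patient stays at −2. State how worsening is then recorded.
- Treat goal 5 separately. Its −1 level is not a clean unchanged level: a patient with no events before or after scores 0 and would gain a level from an automatic −1 baseline. Check that the goal 5 baseline matches the patient's pretreatment event status.
- Re-score any Table 3 goal already entered at −2 before change scores are analysed.

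The cost is about one sentence in section 2.6.2, a matching line in the scoring instructions, and the re-scoring of affected entries. The downside is one level less of measurable gain for the symptoms with most room to improve.
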